### 2.3. Assessment Procedures

#### 2.3.1. Humans Cognitive, Behavioral and Functional Disability Assessment

The RBANS battery [23] will be used for cognitive assessment. This neuropsychological battery measures cognitive decline, even in very mild dementia, or improvement across different domains: Immediate Memory, Visuospatial/Constructional Abilities, Language, Attention, Delayed Memory.HADS [24] will be used for behavioral assessment. It is useful in identifying the anxiety and depression levels of participants.IADL [25] is an appropriate instrument to assess independent living skills at a functional level.The DT [26] protocol assesses the cognitive–motor efficiency when simultaneously performing a cognitive and a motor task. It seems to be a reliable tool even in pre-dementia stages and consists of performing three 2 min tasks, two neutrals (motor task, cognitive task) and the other one with the concurrent tasks.

All these evaluations will be repeated after one-year PEA/placebo treatment and at the follow-up visit.

#### 2.3.2. Biochemical Analyses

Biological samples from subjects at T0, T1 and T2 will be aliquoted, stored at −80 °C until the evaluation of the following biochemical parameters:Apolipoprotein (apo) E genotyping: ApoE genotype of each participant will be determined via PCR, according to standard procedures. Humans have three versions of the APOE gene: ε2, ε3 and ε4 alleles. ApoE genotyping can help estimate a patient’s risk of converting from MCI to AD. In fact, in precedent studies, the epsilon4 allele of apolipoprotein E was considered as the major genetic risk factor for AD onset [27] and conversion to dementia in MCI patients [28].Central and peripheral inflammation: Selected inflammatory markers, specifically altered in MCI and possibly providing predictive information in AD progression, namely, C-reactive protein, interleukin (IL)-6, IL-8, IL-10, monocyte chemotactic protein-1, macrophage inflammatory protein-1beta and soluble triggering receptor expressed on myeloid cells 2, will be evaluated via ELISA and/or the Luminex platform.Amyloid-β, tau and neurofilament light chain: To monitor disease progression and treatment response, neurofilament light-chain protein, Aβ42, total and phosphorylated tau will be quantified via ELISA or using the multiplex Luminex platform.Oxidative stress: The effects of PEA treatment on oxidative/nitrosative stress that occurs at an early stage in AD will be assessed by measuring the presence of 3-nitrotyrosine and 4-hydroxynonenal (two end products of peroxynitrite), through ELISA [29].PEA, AEA and their main catabolic enzymes: The levels of PEA and AEA will be assessed via state-of-the-art liquid chromatography/mass spectrometry. In parallel, enzymatic activity of FAAH and NAAA [5] will be measured via radiometric assays.

## 3. Statistics and Outcomes

### 3.1. Data Analysis

The sample size needed to achieve significant differences was determined based on an a priori power analysis, using the software G*Power 3.1 (Version 3.1.9.4; Program written by Franz Faul, Universatat Kiel, Germany) [30] and published data on changes of Aβ42 levels in CSF of MCI vs. CTRL [31]. For a two-sample *t*-test, accepting a probability of type I error of 5% and a probability of type II error of 20%, required the following sample size for the outcome: Aβ 42 (ngl/mL), delta 42, SD 52, results to be N = 25/group. Based on the above, we propose to enroll 30 subjects per group, with the intent of having 23–25 finishers per group to account for potential dropouts. For the aims of our study, we plan to also enroll 30 control subjects that will be equally distributed within the PEA and placebo arms.

Experimental data will be analyzed using Student’s *t*-test or one- and two-way analyses of variance, followed by Bonferroni post hoc test for multiple comparisons. Differences between the groups will be considered statistically significant at values of *p* < 0.05. Pairwise correlation between variables will be assessed via Pearson’s test and confirmed using Spearman’s rank. Significant outliers will be excluded performing the Grubbs’ test, again, with statistically significant values considered at *p* < 0.05.

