All subjects will be randomly assigned 1:1, with the use of a numeric sequence standard procedure, into treated-with-PEA (composed of 600 mg PEA in capsules; orally, two times per day) or placebo (capsules; orally, two times per day) arms. Both MCI subjects and controls will be divided into two arms: for the MCI group, 25 subjects will be randomized in the PEA arm and 25 subjects in the placebo arm; for control group, 15 controls will be randomized in the PEA arm and 15 in the placebo arm. At the time of enrollment, all participants will be assigned to one of the two main groups (MCI or HC), then they will be assigned a sequential number. Following the random generation sequencing program (www.randomizer.org), each participant will be automatically assigned to one of the two treatment conditions without the direct involvement of any researcher, in order to avoid any personal bias.

Treatment will last for 12 months (T1), followed by a 6-month observational period (T2). All evaluations performed at T0 will be reassessed at T1 and T2.

Aims 2 and 3:

In addition to the above, blood and urine specimens will be obtained from all participants at T0, T1 and T2. All samples will be immediately stored and then analyzed for measuring PEA, its endocannabinoid congeners and other biological markers.

The planned duration of the study is 36 months considering subject enrollment, clinical evaluation, sample collection, treatment duration, post-treatment follow-up, processing, interpretation and result disclosure.

Figure 1 shows the study flowchart.

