### 3.2. Outcomes

For the primary outcome of the study, we expect that PEA administration will decrease the levels of neuroinflammation markers and improve cognitive performance in MCI subjects.

Moreover, for the secondary outcome, we expect to find a reduced conversion from MCI to AD in subjects treated with prolonged PEA administration compared to those within the placebo arm.

For the last outcome, we will also identify the PEA-induced biochemical profile of selected AD targets and its correlation with MCI subjects’ cognitive performance, gaining new insight into biological mechanisms underlying PEA effects on amyloidosis-induced pathology.

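### The 80% power is calculated for a published MCI-versus-control difference in CSF Aβ42, so it is not established for the primary PEA-placebo comparison

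*Protocol article*

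**What the plan says.** Section 3.1 (Data Analysis) takes its inputs from "published data on changes of Aβ42 levels in CSF of MCI vs. CTRL [31"]. For a two-sample t-test with 5% type I and 20% type II error, it names Aβ42 as the outcome and gives "delta 42, SD 52, results to be N = 25/group". It continues that "we propose to enroll 30 subjects per group", "with the intent of having 23–25 finishers per group to account for potential dropouts".

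Section 2.1 (Aims, Design and Setting of the Study) carries the 25 into the randomised comparison: in the MCI group, "25 subjects will be randomized in the PEA arm and 25 subjects in the placebo arm". Aim 1 in the same section compares treated and placebo arms. For the laboratory aims, "blood and urine specimens will be obtained from all participants at T0, T1 and T2".

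Section 3.2 (Outcomes) gives as the primary outcome that "we expect that PEA administration will decrease the levels of neuroinflammation markers and improve cognitive performance in MCI subjects". Selected AD targets come under the last outcome. Section 2.3.2 (Biochemical Analyses) lists Aβ42 with tau and neurofilament light chain, as a marker of progression and treatment response, apart from the inflammatory markers.

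**The concern.** The sample size inputs differ from the trial's primary comparison in three ways.

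- **Contrast.** The inputs describe how people with MCI differ from controls. The trial asks how PEA differs from placebo within MCI. Using the first figure for the second question assumes a treatment effect as large as the whole disease-versus-control gap. The Introduction says that the effectiveness of PEA in MCI has not been explored, and the article offers nothing to support an effect of that size.
- **Fluid.** The inputs are CSF values. No CSF collection is described.
- **Outcome.** Aβ42 is not part of the primary outcome.

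The 80% is the only power figure in the article and the only justification for the arm size. If it does not belong to the primary comparison, a null result could be taken as coming from a test with 80% power when no power has been shown for that test.

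**Working it through.** **Inputs.** Difference 42, SD 52, alpha 5%, power 80% and 23 to 25 finishers per group (section 3.1); 25 per MCI arm (section 2.1). The article does not say whether the test is one- or two-sided. I take two-sided, because one-sided gives 19 (normal approximation) or 20 (t-test), which does not match the stated 25.

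**1. Reproducing the plan's figure.**

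- Standardised difference: d = 42/52 = 0.808.
- Normal approximation: n = 2(1.960 + 0.842)²/d² = 24.06, rounded up to 25 per group.
- Noncentral t: n = 25.06, which strictly rounds up to 26.

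The stated 25 is reproduced within rounding.

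**2. Power for that same d.** The noncentrality parameter is d√(n/2).

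| Per arm | Noncentrality | Power (t-test, two-sided 5%) |
|---|---|---|
| 25 | 0.808 × √12.5 = 2.86 | 79.9% |
| 23 | 0.808 × √11.5 = 2.74 | 76.4% |

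**3. Does the calculation match the trial?**

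| | Sample size calculation (3.1) | Trial's primary comparison (2.1, 3.2) |
|---|---|---|
| Contrast | MCI versus control | PEA versus placebo in MCI |
| Fluid | CSF | Blood and urine |
| Variable | Aβ42 | Neuroinflammation markers and cognitive performance |

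None of the three matches. The article gives no PEA-placebo difference and no SD for any inflammatory marker, cognitive score or blood Aβ42, so a corrected power cannot be computed.

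**4. What the fixed size can detect.** Solving the noncentral-t power equation for the effect at 80% power, for one continuous measure tested at two-sided 5%:

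- 25 per arm: 0.81 SD
- 23 per arm: 0.84 SD

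These figures do not depend on which measure is chosen, but they hold for a single test only. With two primary measures and a Bonferroni split (2.5% each), the detectable effect at 25 per arm rises to about 0.90 SD.

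**5. Illustration for Aβ42 only.** Assume that PEA closes half of the MCI-control gap and that the SD stays at 52. Then d = 21/52 = 0.404, and power is 28.8% at 25 per arm and 26.8% at 23. The share of one half is my assumption; the article gives none. The result does not carry over to inflammatory markers or cognitive scores.

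**The case against.** The strongest defence is that section 3.1 attaches its power openly to Aβ42 and that the arithmetic is right for that variable. Aβ42 is also not foreign to the trial: section 2.3.2 measures it to follow treatment response, and Aim 2 covers neuronal damage markers. All of this stands. It explains why Aβ42 came to mind for sizing, but not why a CSF difference between MCI and controls should stand for a PEA-placebo difference, nor why power for a non-primary marker should justify the arm size.

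One could also read the calculation as meant for MCI versus controls. It would then size a non-randomised comparison and still say nothing about PEA against placebo.

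A reader might infer more, namely that the trial has less than 80% power. The documents do not support that. With no treatment effect or SD for any primary measure, the power there is unknown. It would reach about 80% or more if the true effect on a single tested measure were about 0.81 SD or larger with 25 finishers per arm, and would be lower for smaller effects. The illustration of half the gap cannot settle this, because it rests on an assumed share and concerns Aβ42 alone.

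**Conclusion.** The point holds as a fault in the sample size justification. The stated 80% belongs to a contrast and a fluid that the trial does not use and to a variable outside its primary outcome, so it is not established for the primary PEA-placebo comparison. With the planned 23 to 25 finishers per arm, 80% power requires an effect of about 0.84 to 0.81 SD, which is large, and more if several primary measures share the 5%.

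This assumes a two-sided 5% two-sample t-test on one continuous measure. It does not show that the trial is underpowered, and the arithmetic in section 3.1 is not in error.

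**What to change.** In section 3.1, remove the statement that 25 per group gives 80% power on the basis of CSF Aβ42 in MCI versus controls. Name one primary measure in section 3.2 and replace the power statement with, for example:

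> With 23–25 MCI finishers per arm, a two-sample t-test at two-sided 5% has 80% power to detect a PEA-placebo difference of 0.84–0.81 SD in [the named measure]. Smaller effects are exploratory and will be reported with confidence intervals.

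If more than one primary measure is kept, give the larger detectable effect after multiplicity correction instead (about 0.90 SD at 25 per arm for two measures with Bonferroni). Do not quote a smaller detectable effect from baseline adjustment: section 3.1 plans t-tests and analyses of variance, and the article gives no baseline correlation.

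In the same edit, say whether 25 per arm means randomised or finishing. Section 2.1 randomises 25 per MCI arm, while section 3.1 enrols 30 per group for 23 to 25 finishers.

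**Cost.** One paragraph is rewritten and a primary measure is chosen. No participants, visits or assays are added. The downside is that the stated power looks less favourable.

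### Section 3.1 names only t-tests and one- or two-way ANOVA for outcomes measured three times in the same people, with no baseline adjustment and no method for within-person correlation

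*Protocol article*

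**What the plan says.** Section 2.1 of the protocol article sets T1 at the end of 12 months of treatment and T2 six months later, and states: "All evaluations performed at T0 will be reassessed at T1 and T2". Blood and urine are sampled at the same three times. In the MCI group, "25 subjects will be randomized in the PEA arm and 25 subjects in the placebo arm"; controls are split 15 and 15. Aim 1 is the PEA–placebo comparison after one year, in MCI subjects and in controls.

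Section 3.1 gives the analysis for all experimental data: Student's t-test, or "one- and two-way analyses of variance, followed by Bonferroni post hoc test for multiple comparisons", with significance at p < 0.05. It adds Pearson and Spearman correlations and Grubbs' test for outliers. It does not mention a baseline covariate, a change score, a paired or repeated-measures test, or a mixed model. It also does not say which two factors enter the two-way ANOVA or which visit the t-test uses.

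The sample size rests on a two-sample t-test: "delta 42, SD 52, results to be N = 25/group". On attrition: "we propose to enroll 30 subjects per group, with the intent of having 23–25 finishers per group".

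**The concern.** Three values from one person are correlated, and the T0 value usually predicts the T1 value. The named methods, taken as written, neither use T0 nor allow for the correlation. Two consequences need to be kept apart.

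- **Precision.** A T1-only comparison is valid, but it discards a measurement that the trial has already paid for. With about 25 per arm, and as few as 23 finishers accepted, the planned power has no slack.
- **Error rates.** If the two-way ANOVA were arm by visit, with each visit counted as a new independent observation, the error term would be wrong. The arm test would reject too often. The interaction test, which carries the treatment effect when the arms start level, would reject too seldom.

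The affected comparison is the one-year contrast in Aim 1.

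**Working it through.** **Inputs from section 3.1:** delta 42, SD 52, type I error 5%, type II error 20%, 25 per group, 23–25 finishers. Two-sided testing is assumed because sidedness is not stated. **Input not in the article:** the within-person correlation ρ, so a range is shown. The effect 42/52 is used only because it is the plan's own planning figure.

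**Step 1. Reproduce the stated sample size.** d = 42/52 = 0.808. By the normal approximation, n = 2(1.960 + 0.842)²/0.808² = 24.06, so 25 per group, as stated. The exact t calculation gives 25.06, and power at 25 per group is 79.9%. The stated figure reproduces.

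**Step 2. One comparison at T1, with and without T0.** Adjusting for T0 multiplies the residual variance by (1 − ρ²), so the standardised effect becomes d/√(1 − ρ²). A change score has variance factor 2(1 − ρ). Two-sample t power:

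| Assumed ρ | d/√(1 − ρ²) | T1 only, 25/arm | Change score, 25/arm | ANCOVA, 25/arm | ANCOVA, 23/arm |
|---|---|---|---|---|---|
| 0.3 | 0.847 | 79.9% | 65.7% | 83.5% | 80.2% |
| 0.5 | 0.933 | 79.9% | 79.9% | 89.8% | 87.1% |
| 0.7 | 1.131 | 79.9% | 95.1% | 97.5% | 96.3% |

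At 23 finishers per arm, the T1-only t-test has 76.4% power. ANCOVA reaches 80% power with 23, 20 and 14 per arm at ρ = 0.3, 0.5 and 0.7.

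**Step 3. Type I error of single-value tests.** In 40,000 simulated null trials with 25 per arm, the t-test rejected in 4.8–5.0% at T1 alone and in 4.8–5.0% on change from T0 (ρ = 0.5 and 0.8). Both keep the nominal level.

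**Step 4. Three visits pooled as independent in an arm-by-visit ANOVA.** Suppose equal variances and one common correlation. The variance of an arm mean over three visits is then (1 + 2ρ) times what the pooled error term assumes, so the arm test's false-positive rate is about P(|Z| > 1.96/√(1 + 2ρ)). For the interaction the corresponding factor is (1 − ρ), so that test is conservative. The interaction columns come from simulation (20,000–40,000 trials; runs differ by up to about one percentage point). Power is for an effect of 0.808 SD at both T1 and T2.

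| Assumed ρ | Arm test, false positives | Interaction, false positives | Interaction power, pooled | Interaction power, repeated-measures ANOVA |
|---|---|---|---|---|
| 0.3 | 12% | 1.4% | 50–51% | 69% |
| 0.5 | 17% | 0.3% | 49% | 84% |
| 0.7 | 21% | 0.02% | 45% | 97% |
| 0.8 | 22% | about 0% | 43% | 99.8% |

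Simulation of the arm test agrees with the formula to within about half a percentage point (12%, 17%, 20–21% and 22–23%).

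**The case against.** The strongest reply is that section 3.1 never says visits will be pooled. The design is also a natural two-by-two of diagnosis and arm. A two-way ANOVA of diagnosis by arm at T1, with Bonferroni comparisons, uses one value per person and is valid. A repeated-measures form of the two-way ANOVA is not excluded either. A condensed article may leave factors and covariates to a full protocol or analysis plan that is not shown here.

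Most of this stands. A reader might infer that the plan's error rates are wrong. The text does not support that, because the T1-only, change-score, diagnosis-by-arm and repeated-measures readings all keep the 5% level. Three further inferences also go too far:

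- **That the pooled interaction test is almost powerless.** Its very low rejection rate under no effect is its size, not its power. At the plan's effect its power is about 43–51%, a serious loss but not near zero.
- **That chance baseline imbalance invalidates a T1 comparison.** Under randomisation the standard error already covers it, so it costs precision only.
- **That leaving out ApoE ε4 is an error.** Section 2.3.2 says "ApoE genotyping can help estimate a patient’s risk of converting from MCI to AD", which concerns conversion. It does not make genotype a necessary covariate for continuous scores or markers.

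The reply does not remove the precision point. The article does not leave the analysis open: it commits to named tests, down to the post hoc and outlier procedures, and none of them uses T0. The gain from ANCOVA depends on ρ and on the comparator. It is small at ρ = 0.3, and at ρ = 0.7 it is small against a change score.

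**Conclusion.** The point holds as a loss of precision, with a conditional warning on error rates. At 25 per arm and 0.81 SD, using T0 raises power from about 80% to 83%, 90% or 97.5% for an assumed T0–T1 correlation of 0.3, 0.5 or 0.7. With 23 finishers, the unadjusted test falls to 76%, while ANCOVA stays at 80% or above over the same range. Only if visits are pooled as independent does the arm test's false-positive rate rise to about 12–22% (correlation 0.3–0.8).

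These figures assume two-sided tests, normal data, equal variances and, for the pooled case, a common correlation across visits. The correlations are assumptions throughout. Because the named methods allow choices with such different properties, the analysis should be fixed before the data are seen.

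**What to change.** In section 3.1, replace the general list of tests for the arm comparisons with one stated analysis per continuous outcome. Within the MCI group, and separately in controls, estimate the PEA–placebo difference at T1 with a 95% CI by either:

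- ANCOVA on the T1 value with arm and the T0 value as covariate; or
- a mixed model for T1 and T2 with arm, visit, arm × visit, T0 value and T0 × visit, allowing for within-person correlation (for example, an unstructured covariance) and reporting the adjusted difference at T1.

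State that visits will not be pooled as independent observations. Adjustment for ApoE ε4 is optional; if wanted, name it in advance.

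The cost is a change of wording. T0 values are already collected for every outcome, and no extra participants, visits or assays are needed. The sample size need not rise.

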## 2. Materials and Methods

### 2.1. Aims, Design and Setting of the Study

This study has the following specific aims:Aim 1: To determine if PEA has any effect on neuropsychological, behavioral and functional assessment scores after one-year treatment by comparing treated and placebo arms, both in MCI and control groups;Aim 2: To determine if PEA modifies inflammatory and neuronal damage markers, both at the blood and urine levels in MCI subjects;Aim 3: To determine if these changes correlate with clinical scores in all study participants.

This study will be a double-blind placebo-controlled randomized clinical trial, performed on MCI subjects according to Petersen [18] and the International Working Group for people with amnestic MCI criteria [19]. The initial screening of suitable participants with MCI will take place at outpatient-specific facilities of the “Santa Lucia” Neuroscience and Rehabilitation Foundation (Rome).

Aim 1:

During the recruitment period (0–12 months), an evaluation of the demography, history of concomitant diseases, dietary habits, body mass index (BMI), Mini Mental State Examination (MMSE; [20,21]) and Clinical Dementia Rating scale (CDR; [22]) assessment will be performed for screening all participants, according to the cognitive assessment tools most widely used in Italy. Then, all suitable subjects will be enrolled in the project.

At baseline (T0), a full cognitive, behavioral and functional assessment will be performed by administration of the Repeatable Battery for the Assessment of Neuropsychological Status (RBANS; [23]), Hospital Anxiety and Depression Scale (HADS; [24]) and Instrumental Activities of Daily Living (IADL) questionnaires [25]. Then, a dual-task (DT) protocol will be assessed [26].

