### 2.2. Recruitment and Screening of Participants

Patients will be enrolled in the experimental group according to the following criteria:

Inclusion criteria: aged 60–89 years, possession of the capacity for making decisions, have a reference person (caregiver or companion), be able to read and write in Italian, a MMSE score between 23 and 26.9 points [20,21] and a CDR score < 0.5 [22].

Exclusion criteria: severe physical comorbidity that may limit the execution of the DT protocol, current significant neurological disease (e.g., diagnosis of Dementia, traumatic brain injury, etc.), a current history of alcoholism and/or substance abuse.

A parallel CTRL group of cognitively intact (MMSE score ≥ 27 points [20,21]) age- and sex-matched subjects will be also recruited. Screenings will be conducted by trained physicians and/or neuropsychologists.

We predicted an initial sample of 90 subjects, of which 60 are MCI and 30 CTRL. Then, we hypothesized that the sample size would be reduced due to the inclusion and exclusion criteria (i.e., a worsening in the cognitive functioning corresponding to an MMSE score < 23 points, and a reduced therapeutic adherence, more likely in the MCI group) and possible drop-outs. Therefore, the predicted final sample comprises 80 subjects, of which 50 are MCI and 30 CTRL.

All patients will be informed about the purposes of the research, and all procedures will be carried out with the appropriate understanding and written consent of the subjects, in accordance with the Declaration of Helsinki. Approval of the whole project will be obtained from the Independent Local Ethical Committee.

The inclusion and exclusion criteria are shown in Table 1.

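### The marker–cognition correlations for Aim 3 and the last outcome carry no age adjustment, so a shared dependence on age over 60–89 years could be misread as mechanism

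*Protocol article*

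**What the plan says.** Section 3.1 (Data Analysis) gives the association method in one sentence: "Pairwise correlation between variables will be assessed via Pearson"'s test, with confirmation by Spearman's rank. The group-comparison methods in the same paragraph are Student's *t* "test or one- and two-way analyses of variance, followed by Bonferroni post hoc test for multiple comparisons". None of the named methods has an age term.

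Two parts of the study rely on the correlation method:

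- Section 2.1, Aim 3: "To determine if these changes correlate with clinical scores in all study participants", where the changes are those in the inflammatory and neuronal damage markers of Aim 2.
- Section 3.2, last outcome: the biochemical profile induced by PEA and "its correlation with MCI subjects"' cognitive performance, with the stated purpose of "gaining new insight into biological mechanisms underlying PEA effects on amyloidosis-induced pathology".

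On age, section 2.2 admits patients "aged 60–89 years" and says of the controls that "age- and sex-matched subjects will be also recruited". Age therefore enters the design through eligibility and matching, and is not mentioned again in the analysis.

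**The concern.** A correlation between a marker and a score is an observational comparison across people, even inside a randomised trial. Randomisation balances age between PEA and placebo, but not between participants with high and low marker values. Matching balances age between MCI subjects and controls, but leaves the full spread of age inside each group. The plan regards age as important enough to match on, yet leaves it out of the one analysis where neither matching nor randomisation helps.

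If older participants tend to have higher inflammatory or neuronal damage markers and also lower scores, the two will be negatively correlated through age alone. This can happen within a single diagnosis and a single arm. Spearman's rank checks the shape of the relation and its sensitivity to extreme values. It uses the same unadjusted pairs, so agreement between the two coefficients says nothing about a common cause. At stake is the interpretation: section 3.2 would read these correlations as evidence on how PEA works.

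**Working it through.** **The plan's own figure.** The only computed figure in section 3.1 is the sample size (difference 42, SD 52, 5% and 20% error rates, 25 per group). It reproduces: 2 × [52 × (1.960 + 0.842) / 42]² = 24.06, rounded up to 25. It is not at issue here, and the plan gives no figure for the correlations.

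**Inputs from the document.** Age 60–89 years; 50 MCI subjects (25 per arm) and 30 controls, 80 in all (sections 2.1 and 2.2).

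**Assumptions.** The document gives no correlation of any marker or score with age, so a range is shown. Section 3.1 states no significance level for the correlations; two-sided 0.05 is assumed. Age is taken as uniform over 60–89. Given age, marker and score are independent.

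**Implied correlation.** With marker–age correlation a and score–age correlation −b, the marker–score correlation is −a × b. At 0.3 this is −0.09, at 0.4 it is −0.16, and at 0.5 it is −0.25. The size of r needed for p < 0.05 is 0.279 with 50 subjects and 0.220 with 80.

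**Share of such pairs reaching p < 0.05** (40,000 simulated data sets per setting):

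| Size of age correlation, both variables | Implied r | MCI, n = 50, Pearson | MCI, n = 50, Pearson and Spearman both | One MCI arm, n = 25, Pearson | All, n = 80, Pearson |
|---|---|---|---|---|---|
| 0 | 0 | 5.0% | 3.4% | 5.1% | 5.0% |
| 0.2 | −0.04 | 5.9% | 4.2% | 5.2% | 6.3% |
| 0.3 | −0.09 | 9.4% | 7.1% | 7.0% | 12.6% |
| 0.4 | −0.16 | 20.0% | 16.1% | 11.7% | 29.5% |
| 0.5 | −0.25 | 42.4% | 36.7% | 22.5% | 62.4% |

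**Check by hand for n = 50**, using Fisher's transformation with standard error 1/√47, so √47 = 6.856:

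- At 0.3: atanh(0.09) × 6.856 = 0.62. The chance of passing ±1.96 is about 9.0% + 0.5% = 9.5%.
- At 0.4: atanh(0.16) × 6.856 = 1.11. The chance is about 19.7% + 0.1% = 19.8%.

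Both agree with the table.

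**Where the effect vanishes or shrinks** (n = 50). If only one variable depends on age (0.4 and 0), the share is 4.9%. With 0.5 and 0.1 it is 6.4%. With 0.2 and 0.3, a possible pattern for a change score, it is about 7%.

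**After adjustment.** The partial correlation given age, r(xy·age) = (r_xy − r_x,age × r_y,age) / √[(1 − r²_x,age)(1 − r²_y,age)], is significant in 4.8% to 5.2% of data sets in every setting tested. Only age was simulated; no calculation was made for sex.

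**The case against.** Several points against the concern stand in whole or in part.

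- **This is not a type I error in the strict sense.** A reader might infer that the false-positive rate of the last outcome is well above a stated 5%. The document does not support that. Section 3.1 attaches its 0.05 level to differences between groups and to the outlier test, not to the correlations. And if age drives both variables, the marginal correlation really is non-zero, so detecting it is no false rejection. The problem is confounded interpretation.
- **Aim 3 speaks of changes.** The age link would have to hold for the change in a marker, which may be weaker than for its level; the effect is then small. The last outcome refers to a profile and to cognitive performance, so levels remain a possible reading there.
- **Both age links must be appreciable.** Age-normed RBANS scores would weaken one of them, and the article does not say which scores are used. The MMSE band of 23–26.9 may also weaken the age–cognition link within MCI. The 20% and 42% figures rest on correlations that nothing in the document supports or excludes.
- **The article is condensed.** Covariates may be listed in a fuller plan. This carries less weight, because the article names a specific two-variable method instead of leaving the choice open.

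A reader might also infer that the MCI–control comparisons are faulty for ignoring the matching variables. The article does not say how, or how closely, controls are matched, so that cannot be concluded.

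**Conclusion.** The concern holds as a weakness of the stated method, with a size that cannot be fixed from the document. Unadjusted pairwise correlation over a 60–89 age range can show marker–score links that arise from age alone, and confirmation by Spearman does not guard against this. In 50 MCI subjects the effect is negligible when the age correlations are 0.2 or less, modest at 0.3, and substantial from 0.4 upwards, provided both variables depend on age. The both-tests figure of 7.1% at 0.3 should be set against 3.4% when there is no age effect, so requiring agreement lowers the level without removing the confounding.

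Only Aim 3 and the last outcome are touched. The randomised PEA–placebo comparisons and the sample size are not. The change is worth making because the plan intends to draw mechanistic conclusions from these coefficients and the remedy is almost free.

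**What to change.** In section 3.1, state that inference on marker–score associations will rest on partial Pearson and partial Spearman correlations adjusted for age and sex, or on a linear regression of score on marker with age and sex as covariates. Report the unadjusted coefficients as descriptive only. Sex is included because the plan already matches on it.

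The cost is one sentence. No new data are needed, since demography is recorded at screening and both variables are used for matching. Adjustment takes two degrees of freedom (from 48 to 46 with 50 MCI subjects), and some correlations will look weaker than their unadjusted counterparts.
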